### Analysis

The data collected in this study will be described in terms of mean, standard deviation, median, minimum, maximum and quartiles for continuous variables, while absolute and relative frequencies will be computed for categorical variables. Scores on the applied standardized questionnaires will be calculated according to the user manuals. Frequencies of positive family histories will be reported in combination with confidence intervals.

Exploration of associated variables and group comparisons, e.g. in patients that have undergone or not undergone a colonoscopy, will be performed using logistic or linear regression models as appropriate. All models will be adjusted for relevant confounders. Mixed linear models will be applied in case of paired data or repeated measures.

A detailed description of the statistical methods used in this study will be provided in a Statistical Analysis Plan (SAP) which will be finished before database closure.

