### Study design and setting

FRIDA.Frankfurt is a cross-sectional study in a general practice setting. Prior to the beginning of the study, the practice team (GP and one health care assistant (HCA)) will be briefly trained by study personnel in how to conduct the study in their practices. Before this session, a list of all 40–54 year old patients who have attended the practice within the last twelve months will be compiled by means of the practice software. Afterwards the HCA will contact eligible patients and complete the “Network against colorectal cancer” questionnaire [13] (see screening list, Additional file 1) during a routine practice visit, or per telephone.

Those who have a positive family history will then be invited to participate in the study and to give their informed consent to do so. With the help of study materials that are presented clearly and informatively (both graphic and text based), the GP is expected to be able to provide family members related to CRC patients with adequate evidence-based information and to describe prevention strategies. During this *first practice visit* we plan to examine the participant’s family history of (colorectal-) cancer in further detail, collect information on previous CRC-screening tests, and gather information on other variables (e.g. demographics) associated with an increased risk of CRC (see questionnaire 1, Additional file 2). Study participants with a hereditary risk of CRC (suspected or already known) will be documented and excluded from subsequent study-phases.

In a *second practice visit* within two weeks of the first, details on anxiety, anticipated regret and reasons for or against participation with respect to screening will be collected before the study participants inform their GP about their decision. Furthermore, informed decision will be assessed using the validated instrument from Steckelberg et al. [14]. The selected screening test (colonoscopy, fecal occult blood test) will be documented (see questionnaire 2, Additional file 3).

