### Sample size calculation

As of August 2013, the “Forschungsnetzwerk Allgemeinmedizin Frankfurt” (ForN) [15] database contained approximately 100 general practices. An average-sized practice treats about 1000 patients/quarter of which about 25 % are 40–54 years of age. Over the course of a year, about 250 eligible patients will attend any one practice. It is to be expected that at least 50 % of practices (50) will participate in the study and at least 70 % of patients will complete the questionnaire (175/practice). The expected sample size is at least 8,750 of which about 875 (10 %) are expected to have a positive family history of colorectal cancer [16]. Of these, we expect around 350 (40 %) persons to follow the invitation to have a colonoscopy.

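### The Analysis section makes no provision for clustering of about 175 patients in each of 50 practices; unless the SAP adjusts for practice, the primary confidence interval and regression standard errors would be too narrow

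*Protocol article*

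**What the plan says.** The study is described as cross-sectional: "FRIDA.Frankfurt is a cross-sectional study in a general practice setting". The Sample size calculation works through practices. The research network's "database contained approximately 100 general practices", and half are expected to join. Practice size comes next: "An average-sized practice treats about 1000 patients/quarter of which about 25 % are 40–54 years of age". At least 70% "of patients will complete the questionnaire (175/practice"), which gives 8,750 people, of whom about 10% are expected to have a positive family history. No precision target or design effect is stated.

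Under Study design and setting, each practice team is one GP and one health care assistant. The assistant completes the family history questionnaire with the patients of that practice, at a routine visit or by telephone.

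The Analysis section gives three relevant rules:

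- For the primary outcome: "Frequencies of positive family histories will be reported in combination with confidence intervals". Neither the interval method nor the confidence level is named.
- For associated variables and group comparisons, the analysis "will be performed using logistic or linear regression models as appropriate", adjusted for confounders.
- For dependent data: "Mixed linear models will be applied in case of paired data or repeated measures".

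The section leaves the detailed methods to an SAP due before database closure. Under Fig. 1, further design detail is referred to the full study protocol. Neither document is shown.

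**The concern.** Whole practices are recruited, and within each practice the same assistant asks the question. Practice and interviewer therefore coincide, and any difference between practices in catchment, age mix or manner of asking makes answers within a practice more alike than answers across practices.

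The article itself gives reasons to expect this. The Background reports that family history is partly overstated when patients fill in the form themselves rather than being interviewed, so the primary outcome depends on how it is elicited. It also calls the GP and other medical staff the leading influence on the decision to be screened, so uptake is partly driven at practice level.

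Nesting in practices affects every record, yet it is neither paired data nor repeated measurement, so the stated trigger for mixed models does not reach it. Someone writing the SAP from these rules would fit ordinary regressions and could compute a simple binomial interval. The primary result is one frequency with its interval, and the primary research question refers to a German GP setting, not to these 50 practices alone. Variation between practices is therefore part of the uncertainty that the interval should carry.

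**Working it through.** **The article's own count.** All inputs are from the Sample size calculation.

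- Practices: 100 × 0.50 = 50
- Eligible per practice: 1000 × 0.25 = 250
- Completing per practice: 250 × 0.70 = 175
- Total: 50 × 175 = 8,750
- Positive family history: 8,750 × 0.10 = 875
- Colonoscopies: 875 × 0.40 = 350

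The stated 8,750, 875 and 350 reproduce exactly. This is a recruitment count; no precision or power enters it.

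**Interval if patients were independent** (95% level assumed). SE = √(0.10 × 0.90 / 8,750) = 0.00321. Half-width = 1.96 × 0.00321 = 0.0063, or 0.63 points, so 9.37% to 10.63%.

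**Allowing for practice** (equal cluster sizes). Design effect DE = 1 + (175 − 1) × ICC. Effective n = 8,750 / DE. Half-width = 0.63 × √DE. Coverage of an unadjusted 95% interval = 2Φ(1.96/√DE) − 1. The between-practice SD implied by each ICC is √(ICC × 0.10 × 0.90).

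| Assumed ICC | Between-practice SD (points) | DE | Effective n | Half-width (points) | Coverage of unadjusted interval |
|---|---|---|---|---|---|
| 0 | 0 | 1.00 | 8,750 | 0.63 | 95% |
| 0.001 | 0.95 | 1.17 | 7,453 | 0.68 | 93% |
| 0.005 | 2.12 | 1.87 | 4,679 | 0.86 | 85% |
| 0.01 | 3.00 | 2.74 | 3,193 | 1.04 | 76% |
| 0.02 | 4.24 | 4.48 | 1,953 | 1.33 | 65% |
| 0.05 | 6.71 | 9.70 | 902 | 1.96 | 47% |

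Unequal practice sizes raise these figures. With an assumed coefficient of variation of 0.5 in cluster size and ICC 0.01, DE = 1 + (1.25 × 175 − 1) × 0.01 = 3.18, and the half-width is 1.12 points.

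**Uptake of colonoscopy.** Only family-history-positive patients count here, so the cluster size is 875 / 50 = 17.5 and DE = 1 + 16.5 × ICC. At ICC 0.01 this is 1.17, against 2.74 for the primary outcome. For an uptake of 40%, the independent half-width is 1.96 × √(0.40 × 0.60 / 875) = 3.2 points. At assumed ICCs of 0.05 and 0.10, DE is 1.83 and 2.65, and the half-width is 4.4 and 5.3 points. For analyses restricted to the 350 colonoscopies, clusters average 350 / 50 = 7, and DE at ICC 0.01 is 1.06.

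**The case against.** The strongest reply is that an article may leave variance estimation to the SAP. The interval method is not named, so what is written is compatible with a practice-clustered interval. The article never says that patients will be treated as independent, and never says that mixed models are used only for paired or repeated data. This stands, and it makes the conclusion conditional. A reader might infer that the analysis ignores clustering and that the interval will be too narrow. The documents do not establish either: that would need both an unadjusted interval and a positive ICC, and the article states neither. The point is still more than missing detail, because the section does set out which models apply and when, and those rules leave out the dependence that the sampling creates.

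Three further limits also stand:

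- The mixed-model sentence belongs to the paragraph on associations and group comparisons. It does not govern the primary interval.
- A reader might infer that a linear mixed model is planned for binary outcomes such as family history, neoplasm or uptake. The text does not support this. The sentence concerns paired or repeated data; anxiety and regret, asked about at the second visit and at twelve weeks, are the natural candidates. Logistic regression is available for the binary outcomes.
- No stated figure is falsified. The 8,750 is a feasibility count, and no test or threshold is attached to the primary frequency.

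The ICC range is an assumption. At 0.001 the loss is slight, and nothing in the article fixes the value.

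**Conclusion.** The concern holds in conditional form. The article designs in clusters of about 175 and provides no method for them. If its rules are followed as written and the SAP does not adjust for practice, the primary interval and the regression standard errors would be too narrow under any meaningfully positive ICC. For the primary frequency the correct half-width would be 1.08, 1.37, 1.66 or 2.12 times the unadjusted one (√DE) at an assumed ICC of 0.001, 0.005, 0.01 or 0.02. For uptake, the effect at a given ICC is smaller because clusters are about a tenth of the size.

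This rests on a 95% level, equal cluster sizes, a true frequency near 10% and the assumed ICCs. The point estimate is not in question, and even at ICC 0.05 the interval is about ±2 points around 10%. The change should be made, but the study's value does not depend on it.

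**What to change.** Before database closure, state in the Analysis section or the SAP that:

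1. the primary frequency is reported with a practice-clustered 95% interval, for example by survey linearisation or by GEE with robust standard errors;
2. the regressions use cluster-robust errors or a practice random intercept, in a logistic model for binary outcomes;
3. the estimated ICC for the primary outcome is reported.

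Either choice under items 1 and 2 is sound; what matters is naming it in advance. This takes two or three sentences and no new data, since patients are listed and screened practice by practice. The only downside is a somewhat wider interval.

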### Ethical approval and study registration

Ethical approval for the study was obtained from the leading Ethics Committee at the Frankfurt University Hospital on July 8, 2014. Once the ethical approval has been given by one ethical council in Germany, it applies to all participating sites in the same federal state. The study has been registered in the German Clinical Trials Register; DRKS00006277 [17].

## Discussion

In this cross-sectional study we primarily want to investigate the frequency of positive family history of CRC (1^st^ degree relatives with CRC) among 40–54 year old persons in a German GP setting. Further outcomes are to detect the frequency of colorectal neoplasms (CRC and advanced adenomas) in 1^st^ degree relatives of CRC patients and the kinds of variables that are associated with an increased risk of CRC. In addition, one major objective will be to measure how evidence-based information contributes to making informed decisions with respect to screening and how participation in screening correlates with anxiety and (anticipated) regret.

The role of the GP is an important factor towards screening examinations [7, 8]. It would therefore appear reasonable to expect data that is collected by a specially trained and therefore highly motivated general practice team to be of significantly higher quality. It can further be expected that when professional advice is provided by such a general practice team, colonoscopy participation rates will be higher than otherwise [18], and that this, in turn, will result in an increase in the size of the cohort available to collect information on variables (both demographic variables and biomarkers) for further identification of persons with a positive medical family history. The absence of standardized colonoscopy reports from different gastroenterologists is a potential limitation of this study. Further, variables associated with an increased risk of CRC will be analyzed only among 1^st^ degree relatives of CRC patients. However, this study provides a strong translational context as it involves the creation of new collaborations and synergies involving GPs, clinical epidemiologists and gastroenterologists.

## Abbreviations

CRC: Colorectal cancer
CRF: Case Report Form
DKFZ: German Cancer Research Center
GP: General practitioner
HCA: Health care assistant
IGP: Institute of General Practice
IQWiG: Institute for Quality and Efficiency in Health Care
SOP: Standard operating procedure
